**Methods:**

This prospective, multicenter, comparative observational study includes adults aged 20–65 years presenting with acute LBP within 7 days of onset. Participants undergo a single session of ultrasound-guided Polydeoxyribonucleotide (PDRN) pharmacopuncture targeting the QPI interfascial plane using either a short needle (26G × 60 mm) or a long needle (25G × 100 mm). Group assignment is based on pre-designated site-level data extraction rather than randomization. The primary outcome is the change in the Numeric Rating Scale (NRS) score immediately after treatment. Secondary outcomes include changes in lumbar range of motion (ROM), patient-reported percentage pain reduction (PRPPR), and procedural usability. Safety is monitored immediately post-procedure and again during a telephone follow-up 24–36 h later. Statistical analyses will compare between-group effects and explore potential associations with procedural characteristics.

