**Figure 2 fig2:**
[figure not shown]
Comparison of the two magnetized needle types used in this study (26G × 60 mm and 25G × 100 mm).

All four participating clinical sites routinely use both types of needles in daily practice, depending on actual clinical circumstances. For the purpose of comparative analysis, two sites will be designated to contribute only cases treated with short needles, while the other two sites will contribute only cases treated with long needles. This approach represents a site-level data extraction scheme, rather than a randomized allocation process, and is designed to enable comparative analysis of procedures performed in routine clinical practice without modification of standard patient care.

The study procedures consist of three stages: screening, the treatment visit (Visit 1), and post-procedure follow-up at 24 to 36 h. After providing written informed consent, participants undergo screening, during which demographic characteristics and relevant medical history are collected, and eligibility is assessed based on predefined inclusion and exclusion criteria. Participants who meet all eligibility criteria proceed directly to Visit 1, during which the ultrasound-guided pharmacopuncture intervention and all corresponding study assessments are conducted.

During Visit 1, all enrolled participants undergo a single ultrasound-guided PDRN pharmacopuncture procedure following a standardized protocol. Prior to the intervention, baseline assessments are conducted, including Numerical Rating Scale (NRS) scores for LBP and radiating leg pain, lumbar ROM, the Oswestry Disability Index (ODI), and the Patient-reported Percentage Pain Reduction(PRPPR) score. After the baseline evaluation, the practitioner identifies the interfascial QPI space using high-resolution ultrasonography and then performs the injection using a magnetically guided needle system, administering 1–2 mL of the PDRN pharmacopuncture solution.

The procedure is performed using an in-plane needle approach, enabling real-time visualization of the needle trajectory and tip through ultrasound imaging combined with a magnetic needle-tracking system. Both groups receive the same injection technique and target the same anatomical site; however, the SNG uses a 26G × 60 mm needle, while the LNG uses a 25G × 100 mm needle. All other procedural variables remain consistent across groups.

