During the procedure, performance-related indicators are recorded, including the number of needle insertions, total procedure time, confirmation of needle-tip arrival at the deep target layer (QPI space), and visualization of the hypoechoic spread during injectate delivery. All ultrasound images and needle-tracking log data are stored for subsequent analysis.

Immediately after the procedure, pain intensity (NRS), PRPPR, and ROM are reassessed. Additionally, the operator completes a usability questionnaire to evaluate needle visibility, tracking stability, handling comfort, confidence in target engagement, perceived procedural workload, and overall satisfaction. Any immediate adverse events occurring at this time point are documented in detail.

Follow-up assessments are conducted via telephone within 24 to 36 h after the procedure. During this contact, changes in pain intensity (NRS), PRPPR, functional status in daily activities, and the presence of any delayed adverse events are evaluated. All collected data are recorded using institution-specific Case Report Forms (CRFs) and included in the final analysis after de-identification. A summary of the study procedures is presented in Table 1.

**Table 1 tab1:** Summary of study procedures and assessment timeline.

Study procedure	Period		
	Screening*	Visit 1	F/U^†^
	-1D^‡^	Baseline (0)	~1D
Explanation of the study and obtaining consent	○		
Determination of inclusion/exclusion criteria	○		
Demographic survey^a^	○		
Medical history investigation^b^	○		
ODI (Baseline)^c^		○	
NRS (Pre-/Post-intervention, Day 1)^d^		○	○
PRPPR (Post-intervention, Day 1)^e^		○	○
ROM (Range of Motion) (Pre-/Post-intervention)^f^		○	
Intervention (Short needle vs. Long needle)		○	
Adverse event assessment^g^		○	○

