#### Setting

2.3.1

This multicenter study will take place across four Korean medicine clinics that provide primary outpatient care for musculoskeletal conditions. Participant enrollment and all research-related procedures will be conducted in the outpatient setting of each clinic.

The list of four Korean medicine clinics is as follows:

Kangnyung Korean Medicine Clinic (Anyang, Gyeonggi Province, Republic of Korea).Gwanghwamun Kyung Hee Korean Medicine Clinic (Jongno-gu, Seoul Metropolitan City, Republic of Korea).Mullae Majubom Korean Medicine Clinic (Yeongdeungpo-gu, Seoul Metropolitan City, Republic of Korea).Mapo Hongik Korean Medicine Clinic (Mapo-gu, Seoul Metropolitan City, Republic of Korea).

The interventions will be performed exclusively by Korean medicine doctors who have undergone structured training in ultrasound-guided pharmacopuncture and who are active members of the Academy of Korean Medicine Clinical Anatomy, an organization specializing in ultrasound-based clinical anatomy research.

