#### Statistical analysis

2.6.2

All statistical analyses will be performed using R software (version 4. X. X; R Foundation for Statistical Computing, Vienna, Austria). All tests will be two-tailed, with statistical significance defined as *p* < 0.05. Continuous variables will be summarized as mean ± standard deviation or median with Interquartile Range (IQR), depending on the data distribution. Categorical variables will be presented as frequencies and percentages.

For the primary outcome, changes in NRS scores will be analyzed according to the data distribution. Between-group comparisons will be performed using an independent *t*-test if the normality assumption is satisfied; otherwise, the Wilcoxon rank-sum test will be used. Within-group changes will be assessed using a paired *t*-test or the Wilcoxon signed-rank test, depending on whether the data meet normality assumptions.

For the secondary outcomes, changes in lumbar ROM from baseline will be analyzed using the same statistical methods applied to the primary outcome. Between-group comparisons will be conducted using an independent *t*-test or the Wilcoxon rank-sum test, while within-group comparisons will be analyzed using a paired *t*-test or the Wilcoxon signed-rank test, depending on data normality.

The ODI will be categorized into predefined functional disability levels, and differences in distribution between groups will be analyzed using the Chi-square test or Fisher’s exact test, as appropriate.

PRPPR will be assessed immediately after treatment and again at 24–36 h post-intervention. Between-group comparisons will be conducted using an independent *t*-test or the Wilcoxon rank-sum test, while within-group comparisons will be analyzed using a paired *t*-test or the Wilcoxon signed-rank test, depending on the data characteristics.

In addition, procedural characteristics and usability-related variables associated with needle length—including deep-layer reach success rate, number of insertions, procedure time, and operator usability score—will be summarized using descriptive statistics. When appropriate, exploratory between-group comparisons will be conducted using the Mann–Whitney U test or the Chi-square test. These analyses will serve as supportive reference analyses and will not directly influence the interpretation of the primary clinical outcomes.

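### The between-needle tests named for operator usability and procedural variables assume independent observations, but the data are clustered within operators and sites that each supply one needle only

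*Protocol article*

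**What the plan says.** **Who rates.** Section 2.1 (Study design) says that immediately after the procedure "the operator completes a usability questionnaire to evaluate needle visibility, tracking stability, handling comfort, confidence in target engagement", among other items. There is one rating per procedure, and the rater is the operator, not the patient.

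**How needle relates to site.** The same section says that "two sites will be designated to contribute only cases treated with short needles"; the remaining pair supplies long-needle cases only. Section 2.3.2 (Inclusion criteria) names the two clinics for each needle. Section 2.3.1 (Setting) confirms that "This multicenter study will take place across four Korean medicine clinics". On staff it says only this: "The interventions will be performed exclusively by Korean medicine doctors who have undergone structured training in ultrasound-guided pharmacopuncture". It does not say how many doctors operate.

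**What is tested.** Section 2.6.2 first plans descriptive statistics for deep-layer reach success, number of insertions, procedure time and operator usability score. It then adds, conditional on being appropriate, that "exploratory between-group comparisons will be conducted using the Mann–Whitney U test or the Chi-square test". It calls these analyses supportive and says that they will not directly influence how the primary outcome is read.

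**Status of usability.** The abstract says "Secondary outcomes include changes in lumbar range of motion (ROM), patient-reported percentage pain reduction (PRPPR), and procedural usability". Section 2.1 names procedural usability first among the things to be evaluated. Section 2.5.2, which defines the secondary outcomes, covers ROM, ODI and PRPPR but not usability.

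**The concern.** The Mann–Whitney and Chi-square tests treat every procedure as a separate, independent unit. Scores for handling comfort, visibility or confidence given by one doctor across many cases share that doctor's rating habit. Procedure time, number of insertions and reach success share the doctor's skill and routine. Because each clinic supplies one needle only, these shared components do not cancel between the groups. They add directly to the apparent needle difference.

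Nothing in section 2.6.2 deals with this. Its covariate adjustment is triggered by significant baseline differences between groups, which is a different problem. A fixed site term would not help either, because site determines needle.

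What is at stake is that a difference in habit or skill between the operators at two clinics and those at the other two could be published as a significant effect of needle length on usability or procedural performance.

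**Working it through.** **Inputs from the article**
- Sample size (section 2.6.1): d = 0.56, two-sided alpha 0.05, power 80%, 52 per group, target 60 per group.
- Structure (sections 2.1 and 2.3): four clinics, two per needle, one usability rating per procedure.

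**Inputs not in the article, assumed as ranges**
- Operators per needle, k: 2, 4 or 6 (one to three per clinic), with equal caseloads.
- Within-operator correlation, ICC: 0 to 0.5.
- A five-level usability score.

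**Step 1. The plan's own figure.** By the normal approximation, n = 2(1.96 + 0.8416)²/0.56² = 50.06, so 51 per group. The t-based calculation gives 51.03, so 52 per group and 104 in total, as stated. Allowing 10% dropout, 104/0.9 = 115.6, so 116; the stated 120 rounds this up. The figure of 60 procedures per needle is therefore used below.

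**Step 2. Design effect.** With m = 60/k ratings per operator, DE = 1 + (m − 1) × ICC, and the effective number of ratings is 120/DE. At ICC 0.3:
- k = 2: DE = 1 + 29 × 0.3 = 9.7; 120/9.7 = 12.4
- k = 4: DE = 1 + 14 × 0.3 = 5.2; 120/5.2 = 23.1
- k = 6: DE = 1 + 9 × 0.3 = 3.7; 120/3.7 = 32.4

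**Step 3. False-positive rate.** Normal operator effects plus residual error were rounded to a 1–5 score with no needle effect. The Mann–Whitney test was applied at 0.05 to 60 versus 60 ratings, with 4,000 simulated studies per setting:

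| Operators per needle (ratings each) | ICC 0 | 0.01 | 0.05 | 0.1 | 0.3 | 0.5 |
|---|---|---|---|---|---|---|
| 2 (30) | 5% | 8% | 20% | 31% | 53% | 63% |
| 4 (15) | 5% | 6% | 12% | 20% | 39% | 47% |
| 6 (10) | 5% | 5% | 10% | 15% | 29% | 39% |

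The Monte Carlo standard error is at most √(0.25/4000) = 0.8 percentage points. Repeat runs move the entries by a point or two, so the ranges are best read as about 9–20% at 0.05, 14–32% at 0.1 and 29–54% at 0.3.

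**Step 4. Analytic cross-check.** The rate is approximately 2[1 − Φ(1.96/√DE)].
- k = 2, ICC 0.1: DE = 3.9, 1.96/1.975 = 0.992, giving 32%.
- k = 6, ICC 0.3: DE = 3.7, 1.96/1.924 = 1.019, giving 31%.

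Both agree closely with the simulation. The other three variables were not simulated. The same design-effect reasoning applies to them, with their own unknown correlations.

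**Step 5. The level at which needle is fixed.** Ranking two clinics against two gives 6 arrangements, so the smallest two-sided p-value is 2/6 = 0.33. A rank comparison at clinic level therefore cannot reach 0.05, whatever the number of operators.

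**The case against.** The strongest defence is the status of these analyses. They are descriptive first, tested only where appropriate, labelled exploratory, and kept apart from the primary outcome. Section 2.5.2 does not list usability among the secondary outcomes. This stands and limits the consequence. It does not make the named tests fit the data, and section 2.1 and the abstract both give usability more weight than a side analysis.

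The second defence is that the size is unknown, because the number of operators and the correlation are not given. This also stands. One operator per clinic is the worst case, so a range is needed. If the correlation were close to zero the tests would be about right. For subjective scores given repeatedly by one person that is unlikely, but the article has no figure to settle it.

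Three stronger readings are tempting, and the article does not support them:
- **That the true sample size is simply the number of operators.** Ratings also vary with the patient. Section 3 (Discussion and conclusion) names body habitus and muscle thickness as sources of technical difficulty, so repeat ratings are not duplicates. Even in the worst case above at ICC 0.3, about 12 effective ratings remain, against 4 operators.
- **That operators use only one needle in practice.** Section 2.1 says all four sites routinely use both. The restriction is on which cases each site contributes.
- **That needle-selection criteria will rest on these p-values.** The abstract says that clinical and procedural results together may contribute to such criteria, as preliminary evidence before randomised trials.

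Needle is nested in site for the primary NRS comparison too. That is a separate question and is not sized here.

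**Conclusion.** The point holds for the four procedural and usability variables. The article names tests that need independent observations for data that, on its own description, are clustered within operators and sites nested in needle, and no part of the analysis section accounts for this. This is a mismatch in what the article fixes, not a detail left to a fuller document.

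Under the stated assumptions the false-positive rate at a nominal 5% runs from about 9% (six operators per needle, correlation 0.05) to about 54% (two operators per needle, correlation 0.3). More operators or a smaller correlation would reduce the inflation; correlation between operators at the same clinic would add to it. The calculation takes each operator to work on one needle only within the study data, which follows if each works at a single clinic.

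The damage is confined to the supportive conclusions on usability and procedure. A reader might infer that the primary result is compromised by this sentence; section 2.6.2 explicitly separates the two.

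**What to change.** In section 2.6.2:
1. Keep the planned descriptive summaries for all four variables: usability score, procedure time, number of insertions and deep-layer reach success.
2. Present each by operator and by site beside the pooled figure for each needle.
3. Delete the sentence allowing pooled Mann–Whitney or Chi-square comparisons of these variables.
4. State that, because each site contributes one needle only, a needle effect on these variables cannot be separated from operator and site.

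If a formal comparison is still wanted, operator-level summaries or a model with an operator random effect would respect the clustering. Either would have to be reported with a warning about the very small number of clusters, and neither would remove the confounding with site.

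The cost is a few sentences and one table. The table needs the operator to be identifiable for each procedure. No additional patients and no change to care are required. The downside is that there will be no p-value for these exploratory variables.

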#### Sample size calculation

2.6.1

Since no prior study has been conducted under conditions identical to the present trial, the effect size for this study was estimated based on comparable interventions and studies reporting changes in NRS or VAS as primary outcomes. In a double-blind randomized controlled trial evaluating pharmacopuncture in patients with chronic LBP, the mean reduction in pain after 3 weeks was 2.74 points in the treatment group and 1.76 points in the control group, yielding an estimated between-group difference of approximately 1.0 point and a Cohen’s d of approximately 0.56 (23). Similarly, a systematic review of acupuncture for acute LBP reported a mean difference of −1.75 points on the VAS compared with controls (95% CI: −2.39 to −1.12) (24), indicating a meaningful short-term analgesic benefit. Additionally, a single-arm study conducted in Japan evaluating ultrasound-guided hydrodissection demonstrated a reduction of more than 4 points on the VAS immediately after the procedure (25), suggesting that ultrasound-guided interventions may provide rapid short-term pain relief.

Additionally, although the Minimum Clinically Important Change (MCIC) for acute LBP has been reported to be approximately 3.5 points on the NRS scale (26), such thresholds primarily apply to single-arm studies evaluating absolute symptom improvement. In comparative trial designs, such as the present study, the full magnitude of the MCIC is not required to determine a meaningful treatment difference. Instead, between-group differences of approximately 1 point—similar to those reported in previous randomized controlled trials—may still represent a clinically relevant effect when assessing comparative therapeutic outcomes.

Based on the literature reviewed, the effect size for this study was set at Cohen’s d = 0.56. Using a two-sample *t*-test with a significance level of 0.05 and a statistical power of 80%, the minimum required sample size was calculated to be 104 participants (52 per group). Allowing for an anticipated dropout rate of approximately 10%, the final target sample size was set at 120 participants, with 60 allocated to the short-needle group and 60 to the long-needle group.

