If significant baseline differences are identified between the two groups and these variables are considered potentially related to the outcome measures, they will be treated as possible confounding factors. In such cases, subgroup analyses or multivariate analyses (e.g., ANCOVA or multiple regression models) will be conducted. Adjusted effect sizes with corresponding 95% confidence intervals will be reported to improve the interpretability and accuracy of the findings.

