Despite these strengths, this study has several inherent limitations due to its exploratory observational design. First, the site-based allocation approach may introduce selection bias. Second, because the intervention was conducted as a single session with short-term follow-up (24–36 h), the study design does not permit evaluation of sustained or cumulative treatment effects. Third, not all participants underwent imaging-based diagnostic confirmation, which may lead to diagnostic heterogeneity and should be taken into account when interpreting the findings.

Future research should include randomized controlled trials to verify the independent effects of needle length and NGS application, as well as quantitative imaging-based assessments of needle tip visibility and tracking accuracy. Additionally, studies incorporating repeated interventions, long-term follow-up, and subgroup analyses based on BMI, muscle thickness, or pain phenotype may further clarify patient-specific treatment responses. Finally, cost-effectiveness analyses would help determine the practical value of ultrasound-guided interfascial pharmacopuncture in primary care settings and contribute to establishing clearer clinical indications and standardized application criteria for the QPI-guided approach.

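### Adjustment for confounders depends on a baseline significance test, which is more likely than not to miss imbalances below about 0.36–0.39 SD in this non-randomised comparison

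*Protocol article*

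**What the plan says.** Under 2.6.2 Statistical analysis, the primary between-group comparison of NRS change is an independent t-test if normality holds; "otherwise, the Wilcoxon rank-sum test will be used". Neither test uses a covariate. For the whole plan, "All tests will be two-tailed, with statistical significance defined as" p < 0.05.

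Adjustment comes in the last paragraph of that section and has two conditions: "If significant baseline differences are identified between the two groups and these variables are considered potentially related to the outcome measures". Only then are the variables treated as possible confounders, and "In such cases, subgroup analyses or multivariate analyses (e.g., ANCOVA or multiple regression models) will be conducted". Adjusted effect sizes with 95% confidence intervals are promised for that case.

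The abstract says of the design: "Group assignment is based on pre-designated site-level data extraction rather than randomization". Section 2.1 explains that all four clinics use both needles in daily practice, but two contribute only short-needle cases and two only long-needle cases. The Discussion concedes: "First, the site-based allocation approach may introduce selection bias".

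**The concern.** In a randomised trial, baseline differences arise by chance. Here they are expected, because the two groups are different patients at different clinics. What a covariate does to the comparison is set by how far the groups differ on it and how strongly it predicts NRS change. A baseline p-value measures neither; it mixes the size of the imbalance with the sample size. With 52–60 patients per group, a moderate imbalance will often be non-significant and therefore ignored.

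The second condition, a judgement that the variable is related to outcome, can only narrow the set further. Together they make the choice between an adjusted and an unadjusted result depend on the observed baseline data. The rule also lists subgroup analyses as an alternative to multivariable adjustment, although separate subgroup results do not by themselves give an adjusted overall difference. At stake is measured confounding left in the primary estimate when the data to remove it are already on the case report form.

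**Working it through.** **Inputs from the documents.** Effect size: "the effect size for this study was set at Cohen’s d = 0.56" (2.6.1), two-sided alpha 0.05, power 80%, 52 evaluable and 60 recruited per group. The cited reductions of 2.74 and 1.76 points differ by 0.98, so the implied SD of NRS change is 0.98 / 0.56 = 1.75 points.

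**The plan's own figure.** A two-sample t-test with d = 0.56 needs 51.03 per group by the exact noncentral t, rounded up to 52. Power at 52 is 80.7%. 104 / 0.90 gives 116 after rounding up, and the plan takes 120. The sample size reproduces.

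**Inputs assumed.** The documents give neither the size of any imbalance nor any covariate–outcome correlation. Both are varied below.

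**Step 1: chance that the baseline test flags a true imbalance** (noncentral t, two-sided 0.05).

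| True imbalance (SD) | 60 per group | 52 per group |
|---|---|---|
| 0.2 | 19% | 17% |
| 0.3 | 37% | 33% |
| 0.4 | 58% | 52% |
| 0.5 | 78% | 71% |
| 0.6 | 90% | 86% |

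The chance reaches 50% at 0.36 SD (60 per group) or 0.39 SD (52 per group). It reaches 80% only at 0.52 or 0.55 SD, close to the planned treatment effect of 0.56.

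**Step 2: bias if no adjustment is ever made.** Bias = imbalance × correlation × SD. At 0.30 SD this is 0.30 × 0.3 × 1.75 = 0.16 points, and 0.26 and 0.37 points for correlations 0.5 and 0.7.

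**Step 3: bias left when the test does not flag.** Studies that escape the flag have a smaller observed imbalance than average, so Step 2 overstates the bias in them. With 60 per group, the standard error of the observed imbalance is s = √(2/60) = 0.183, and the flagging threshold is 1.980 × 0.183 = 0.362. For a true imbalance of 0.30:

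- Standardised upper limit: (0.362 − 0.30) / 0.183 = 0.337. The lower limit is negligible.
- Probability of no flag: Φ(0.337) = 0.63.
- Mean observed imbalance given no flag: 0.30 − 0.183 × φ(0.337) / Φ(0.337) = 0.30 − 0.183 × 0.377 / 0.632 = 0.191 SD.
- Mean bias = correlation × 0.191: 0.057, 0.096 and 0.134 SD for correlations 0.3, 0.5 and 0.7.
- Times 1.75: about 0.10, 0.17 and 0.23 NRS points, or 10%, 17% and 24% of 0.98.

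Simulation of the test-then-adjust rule agrees to within 0.01 SD.

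**Step 4: effect on type I error** (simulation, no needle effect, 60 per group). With one covariate the rule as a whole gives 4.6–6.9% across imbalances of 0.2–0.6 SD and correlations of 0.3–0.7; at 0.30 SD and correlation 0.5 it is 6.0%. With three to five covariates all favouring the same group (0.2–0.3 SD, correlation 0.3 each) it gives 7.8–16.9%, with mean bias of 0.10–0.18 SD (0.18–0.32 points). Always adjusting gives 4.5–5.4% in every setting.

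**The case against.** The strongest reply is that the rule catches the worst cases. That stands: above about 0.36–0.39 SD the test flags more often than not. A reader might infer that it misses most imbalances that matter; the calculations do not support this. Nor do they show that the reported result will usually be unadjusted. With three independent covariates each imbalanced by 0.30 SD, at least one is flagged in 1 − 0.629³ = 75% of studies, before the relevance condition is applied.

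Three further inferences go beyond the documents. Outcome assessors are stated to be unblinded (2.5.2.3), but nothing says whether whoever chooses the model is. The Discussion names body habitus as a source of technical difficulty, and 2.1 says needle use depends on clinical circumstances; neither makes habitus a selection rule. And 2.3.6 refers to a predefined statistical analysis plan that is not shown, so the lack of a covariate list in the article is not itself a fault.

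Subgroup analysis can also be defended: stratifying on a confounder and combining the strata is a valid adjustment, and adjusted effect sizes are promised. The fair criticism is only that separate subgroup results must not replace an adjusted overall estimate.

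Finally, the study calls itself exploratory and admits possible selection bias. That limits what will be claimed but does not justify the trigger, which is a rule the article states, not a detail left to another document.

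**Conclusion.** The concern holds in limited form. Making adjustment conditional on a significant baseline difference is a poor rule for a site-allocated comparison, because moderate imbalances are more likely than not to go unadjusted. For one covariate imbalanced by 0.30 SD, the bias left in unflagged studies averages 0.06–0.13 SD, about 0.10–0.23 NRS points. This rests on assumed correlations of 0.3–0.7 and the implied SD of 1.75. The cost is mainly bias: one covariate barely moves type I error, and a material rise needs several imbalances in the same direction, which is also an assumption.

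A reader might infer that covariate adjustment would make the comparison unconfounded. It would not. Each site contributes one needle type, so site and operator differences cannot be separated from needle length by any patient-level model.

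**What to change.** In 2.6.2, delete the significance trigger. Make the primary analysis a regression (ANCOVA) of post-procedure NRS on needle group with pre-specified covariates: baseline NRS, age, sex, BMI from height and weight, baseline ODI, and symptom duration if recorded. Fit it whatever the baseline p-values. With baseline NRS in the model, the group coefficient is the same whether the outcome is the post-procedure score or the change, so the primary outcome need not be redefined.

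Report the adjusted difference with its 95% confidence interval and keep the unadjusted t-test or Wilcoxon test as a sensitivity analysis. State that separate subgroup analyses do not stand in for the adjusted overall estimate. State also that no site term can be added under the present design, so site and operator confounding remain.

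The cost is 5–6 degrees of freedom out of 120 patients and a change of wording. Apart from symptom duration, which Table 1 does not list as a data item, all these variables are already collected. Section 2.1 says that nobody had been recruited when the manuscript was submitted.
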